# INTRAGO: intraoperative radiotherapy in glioblastoma multiforme – a Phase I/II dose escalation study

**DOI:** 10.1186/1471-2407-14-992

**Published:** 2014-12-22

## Abstract

**Background:**

Glioblastoma multiforme (GBM) is the most frequent primary malignant brain tumor in adults. Despite multimodal therapies, almost all GBM recur within a narrow margin around the initial resected lesion. Thus, novel therapeutic intensification strategies must target both, the population of dispersed tumor cells around the cavity and the postoperative microenvironment. Intraoperative radiotherapy (IORT) is a pragmatic and effective approach to sterilize the margins from persistent tumor cells, abrogate post-injury proliferative stimuli and to bridge the therapeutic gap between surgery and radiochemotherapy. Therefore, we have set up INTRAGO, a phase I/II dose-escalation study to evaluate the safety and tolerability of IORT added to standard therapy in newly diagnosed GBM. In contrast to previous approaches, the study involves the application of isotropic low-energy (kV) x-rays delivered by spherical applicators, providing optimal irradiation properties to the resection cavity.

**Methods/Design:**

INTRAGO includes patients aged 50 years or older with a Karnofsky performance status of at least 50% and a histologically confirmed (frozen sections) supratentorial GBM. Safety and tolerability (i.e., the maximum tolerated dose, MTD) will be assessed using a classical 3 + 3 dose-escalation design. Dose-limiting toxicities (DLT) are wound healing deficits or infections requiring surgical intervention, IORT-related cerebral bleeding or ischemia, symptomatic brain necrosis requiring surgical intervention and early termination of external beam radiotherapy (before the envisaged dose of 60 Gy) due to radiotoxicity. Secondary end points are progression-free and overall survival.

**Trial registration:**

The study is registered with clinicaltrials.gov, number: NCT02104882 (Registration Date: 03/26/2014).

## Background

Despite recent advances in therapy, Glioblastoma multiforme (GBM) is a lethal disease in most cases with a relatively short overall survival of roughly 15 months
[1, 2]. In virtually all cases, GBM recur locally within a narrow margin (2–3 cm) around the tumor cavity
[3–5]. Although GBM are highly invasive and able to migrate along pre-existing structures such as blood vessels or white matter tracts
[6, 7] most (if not all) recurrent tumors paradoxically grow in close proximity to the resection margin
[8]. Thus, though novel surgical techniques (such as fluorescence-guided resection) may have improved the rates of macroscopic complete resections
[9], and advanced radiotherapy techniques are at hand, no single or combined approach is sufficient to deplete microscopically dispersed tumor cells around the tumor cavity.

One of the techniques employed to tackle this challenging feature of GBM is intraoperative radiotherapy (IORT). IORT allows the delivery of high doses of electrons (IO*E*RT) or low energy x-rays to the tumor bed while the surrounding healthy tissue is spared from radiation due to steep dose gradients
[10]. This could lead to instant sterilization of the cavity surface from remaining tumor cells and delayed, or impaired, tumor cell proliferation between surgery and adjuvant therapies in deeper areas receiving lower doses. Furthermore, high single doses may elicit local (tumor bed) and systemic (immunogenic) responses which are not observed in this extent after conventionally fractionated radiotherapy
[11, 12].

Several, mostly small retrospective single-institutional studies have shown efficacy of the approach (reviewed in
[13]). However, those pioneering studies were using IOERT and thus faced classical technical challenges that come along with a forward-scattering irradiation system in a setting with cylindrical or spherical tumor cavities. Postoperative dose reconstructions from the Munster University group demonstrated that many patients receiving IOERT exhibited areas of inadequate coverage (due to inaccurately selected electron energies, inappropriate cone sizes or angle errors). As expected, they found that median and 2-year survival significantly improved with better coverage (MS: 15.2 with adequate coverage *vs*. 9.3 months with inadequate coverage; 2-year survival: 9.3% *vs*. 0%, p = 0.02)
[14, 15].

In contrast to the previously used forward-directed electron beams, the isotropic low-energy X-ray irradiation source used in the TARGIT (TARGeted Intraoperative radioTherapy) trial for breast cancer (INTRABEAM system)
[16] is specifically attractive in IORT for brain tumors, where post-resection cavities are normally of complex shape. IORT using such spherical applicators has been proven feasible in pediatric
[17] and adult primary brain tumors
[18, 19]. However, as there are no prospective data on safety and tolerability of IORT, we have designed INTRAGO, a phase I/II study built on the experience from past trials in several of which proof-of-principle has been demonstrated.

## Objectives

### Primary objectives

The primary goal is the definition of the maximal tolerated dose (MTD) of spherical isotropic kV-IORT in the setting of primary GBM.

### Secondary objectives

Secondary endpoints are progression-free (PFS) and overall survival (OS).

## Methods/Design

INTRAGO resembles a prospective, open-label, single-arm dose-escalation study (Figure 
1). Dose escalation will be conducted in a “classical” 3 + 3 manner with three patients entering each dose level. The decision to escalate to the next dose level is based on safety assessments after all patients of a cohort have reached month 3 (90 days) after IORT: If no dose-limiting toxicities (DLTs) occur in a cohort of 3 patients, the next cohort of 3 patients will be treated at the next higher dose level. If one of the 3 patients in a cohort experiences a DLT, an additional cohort of 3 patients will be treated at the same dose level: If no DLT occurs in the additional cohort, dose escalation will continue at the next higher dose level. Should one or more of the 3 patients in the additional cohort experience a DLT, the MTD is considered exceeded and dose escalation will stop. The preceding dose level will then be considered as the MTD. If two or all of the 3 patients in a cohort experience DLTs, the MTD will be considered exceeded and the preceding dose level will be defined as the MTD. If only a total of 3 patients were treated at the potential MTD level, the potential MTD needs to be confirmed by recruiting an additional cohort of 3 patients: If none or one of the 6 patients experience a DLT, the MTD will be considered confirmed. If two or more patients experience a DLT, the next lower dose level will become the potential MTD. If no DLT occurs at all, the highest dose level will be defined as the MTD. Thus, the MTD is defined as the highest dose at which one or no DLT will have been observed among 6 patients.

**Figure 1 Fig1:**
[figure not shown]
**Study Workflow.** Legend: KPS, Karnofsky Performance Status; GBM, glioblastoma multiforme; LENT-SOMA, Late Effects in Normal Tissues - Subjective, Objective, Management and Analytic (LENT-SOMA). IORT, intraoperative radiotherapy; EBRT, external beam radiotherapy; DLT, dose-limiting toxicity; MRI, magnetic resonance imaging.

## Patient selection

Patients aged 50 years or older with a Karnofsky performance status (KPS) of at least 50% and a histologically confirmed (frozen sections) supratentorial unifocal GBM are included. The tumor location should allow maximum safe resection. However, patients with tumors that are likely to be only partially removable are also eligible for the study.

### Inclusion criteria

Histologically confirmed glioblastoma multiforme in frozen sectionsAge ≥50 yearsKarnofsky Performance Index ≥ 50%Written Informed consentAdequate birth control (e.g., oral contraceptives)

### Exclusion criteria

Astrocytoma ≤ WHO grade IIIGliomatosis cerebriMultifocal lesionsInfratentorial localizationPrevious cranial radiation therapy (any location)Uncontrolled intercurrent illnesses including, but not limited to, ongoing or active infection or psychiatric illness/social situations that would limit compliance with study requirements.Contraindications for general anaesthesiaBleeding or clotting disordersContraindications for MRI or CT scansPregnant or breastfeeding women

## Assessment of the primary objective (Safety)

The primary goal is to determine the MTD, which will be assessed on the basis of pre-defined dose-limiting toxicities (DLT).

Two types of DLT are defined:Early DLTs (≤3 weeks after IORT):wound infections/wound healing difficulties requiring surgical interventionIORT-related cerebral bleeding or ischemia2)Early-delayed DLTs (≤3 months after IORT):Symptomatic brain necrosis requiring surgical interventionEarly termination of EBRT (before the envisaged dose of 60 Gy) due to radiotoxicity

DLTs will be assessed on the basis of clinical presentation (physical examination, KPS, current medication), imaging studies (MRI) and on the basis of a neurological assessment using the *Late Effects in Normal Tissues Subjective, Objective, Management and Analytic* (LENT-SOMA) scales defined by the EORTC/RTOG
[20, 21].

### Evaluation of DLT: clinical exams, medication

Each follow-up visit has to include the most recent medical history, an inspection of the wound/scar and a thorough clinical exam. Episodes of partial or complex seizures must be documented. Wound healing (and the scar at FU) is followed with photo documentation. When performing a physical exam, there should be a specific emphasis on neurological functions. Specific awareness is advised for signs of cerebral edema (for example alterations in the level of consciousness, bradycardia, high blood pressure or inequality of pupillary size). All current medication and all changes made in the medication schedule have to be documented. Detailed information on doses (and dose changes) has to be only documented for corticosteroids and anticonvulsants.

### Evaluation of DLT: MRI

Each follow-up visit includes MRI with contrast-enhanced (gadolinium) T1, axial T2 and axial T2-FLAIR sequences. Ischemic areas can be delineated using perfusion diffusion-weighted imaging. It is challenging to distinguish early post-treatment blood–brain barrier permeability impairment from tumor recurrence and “true” brain necrosis. Here, methods such as *Lesion Quotient* (LQ), which resembles a ratio of the area delineated in a T2 sequence and the area of the corresponding contrast-enhanced T1 sequence may be applied
[22]. In case MRI scans are inconclusive, positron emission tomography with amino acid tracers (such as ^18^F-fluoro-ethyl-tyrosine) can be offered as preferential modality.

## Management of DLT

Wound infections must be adequately treated, e.g. with dry absorbent dressing and, in case of positive wound swabs, systemic antibiotics should be administered matching to the antibiogram. In all cases of wound infection, blood workup (Complete blood counts, white blood counts, CRP) and imaging studies should be performed (CT or MRI) to rule out intracranial abscesses. Each case of wound infection (our healing difficulty) where conservative therapy fails and surgical revision is required is defined as DLT.

Due to the highly flexible positioning system of the IORT device, cases of cerebral ischemia or bleeding induced by the applicator are unexpected. Nevertheless, both were included into the protocol as DLTs and cases where (venous or arterial) ischemia or intracranial haemorrhage occur as a consequence of the IORT procedure (addition to the baseline risk), adequate therapy is required. Intracranial haemorrhages must be generally surgically removed if mass effects are exceeding the primary lesion volume. There is no symptomatic therapy for arterial or venous ischemia post resection. However, diffusion-weighted imaging (DWI) should be performed to document these events during follow-ups.

If radiation necrosis is suspected in MRI scans and no correlating clinical deterioration is noted, symptomatic therapy may not be necessary and observation is appropriate. For patients with mass effects or neurological symptoms, treatment options include conservative therapy with corticosteroids or anti-angiogenic substances (e.g., bevacizumab) or surgical debulking of the necrotic areas. The decision for either therapy should be made in interdisciplinary consensus (e.g., in interdisciplinary tumor boards). If surgery is required, the corresponding case will be defined as DLT.

All patients will undergo radiochemotherapy and will present five times per week at the linear accelerators. Complete blood counts (CBC), a chemistry panel, liver function tests (LFT) as well as renal function tests (RFT) are regularly performed to screen for hematotoxicity, hepatotoxicity or renal toxicity under temozolomide chemotherapy. Upon intolerance, incompliance or deterioration of CBCs, LFTs or RFTs, the therapy with temozolomide can be discontinued at any time point by any physician in charge. Any discontinuation of chemotherapy for more than 5 consecutive days has to be documented.

Cranial irradiation can elicit acute (side) effects occurring during treatment or early-delayed effects that appear within three months after radiochemotherapy
[23]. In most cases, both acute and early delayed side effects largely resemble symptoms of mass effects (e.g., headache, nausea, worsening neurological symptoms), they are responsive to corticosteroids and they either gradually decrease in severity during daily radiotherapy (acute effects) or spontaneously resolve under cortisol (early-delayed). However, any case of radiotherapy-associated symptom deterioration that requires pausing of radiotherapy for more than 5 consecutive days has to be documented. If radiotherapy is entirely discontinued due to radiotherapy-associated side effects before the total dose of 60 Gy is reached, the case is considered to exhibit a DLT. As for chemotherapy, EBRT may be discontinued by any physician in charge.

## Assessment of secondary end points (efficacy)

Secondary end points are progression-free (PFS) and overall survival (OS). PFS is defined as the interval (in days or months) from IORT to the date of first detection of progressive disease according to updated RANO criteria
[24] or the date of last follow-up. The RANO working group recommended tight restrictions for evaluating progression within 12 weeks after radiotherapy as irradiation transiently increases the permeability of the (peri)tumoral vasculature which in turn impairs the validity of MRI scans during this period
[25].

In INTRAGO, only cases where new T1-enhancing lesions are detected *beyond* the 80% isodose or new lesions that are histologically proven to be new manifestations of GBM are defined as true progression within a timeframe of 12 weeks after EBRT.

After this period, progressive disease is defined if one of the following RANO criteria applies:New T1-contrast-enhancing lesions outside of radiation field on decreasing, stable, or increasing doses of corticosteroidsIncrease by ≥ 25% in the sum of the products of perpendicular diameters between the first post-radiotherapy scan, or a subsequent scan with smaller tumor size, and the scan at 12 weeks or later on stable or increasing doses of corticosteroids.Clinical deterioration attributable to tumor progress (and not to concurrent medication or diseases)Increased T2/FLAIR compared with baseline scan or best response after initiation of therapy on stable or increasing doses of corticosteroids.

OS is defined as the interval (in days or months) from IORT to the date of death from any cause.

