### EBRT

EBRT must be initiated within 4 weeks after surgery and IORT. All patients will receive five fractions of radiotherapy per week on a conventional linear accelerator (LINAC) with thermoplastic mask fixation. Pausing of radiotherapy is allowed for maximum 5 consecutive days. During EBRT, patients are routinely seen once to twice weekly by physicians and evaluated for adverse reactions.

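### PFS is defined without death as an event, so as written it is time to progression and may read too long

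*Protocol article*

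**What the plan says.** Under *Assessment of secondary end points (efficacy)*, the protocol article runs PFS "from IORT to the date of first detection of progressive disease according to updated RANO criteria" and gives one alternative end date, "or the date of last follow-up". No third stopping point is named. The same section states: "OS is defined as the interval (in days or months) from IORT to the date of death from any cause".

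That section also restricts what counts as progression early on. Only new enhancing lesions outside the 80% isodose, or lesions "histologically proven to be new manifestations of GBM are defined as true progression within a timeframe of 12 weeks after EBRT", qualify. A wider list of criteria opens once that window has closed, and it includes "Clinical deterioration attributable to tumor progress (and not to concurrent medication or diseases". Death is not on either list.

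Under *Secondary objectives*, PFS and OS are the two secondary endpoints. The primary objective is the MTD.

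**The concern.** PFS ordinarily counts death before progression as a failure. Here the only place for such a death is the last follow-up date, alongside patients who are alive and free of progression. A death then leaves the risk set without lowering the curve.

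Such deaths are possible in this trial. *Background* calls the disease lethal in most cases, with overall survival of roughly 15 months. *Patient selection* admits patients aged 50 or older with a Karnofsky status down to 50%. *Serious adverse events* foresees fatal IORT-related events. In the first months a patient can decline and die without meeting the narrow early definition of progression.

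At stake is how one of the two efficacy endpoints is read. The quantity reported as PFS would not be progression-free survival, and any gap between the two would favour the treatment.

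**Working it through.** The article states no PFS rate, event count or sample size for PFS, so there is no figure to reproduce. The check covers the wording, the early window, and the direction and size of the effect.

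**1. Wording.** PFS ends at progression or last follow-up. OS ends at death. Neither list of progression criteria includes death. A death without documented progression therefore has no place in the PFS definition except last follow-up.

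**2. Length of the restricted window.** *EBRT* says "EBRT must be initiated within 4 weeks after surgery and IORT" and gives five fractions per week. The treatment-planning section gives 30 fractions, so EBRT takes 30/5 = 6 weeks without pauses. The restricted rule then applies for 12 weeks after EBRT. With the latest permitted start, the wider criteria open at 4 + 6 + 12 = 22 weeks after IORT, and later if EBRT is paused. Until then, clinical deterioration attributed to tumour is not a listed route to progression.

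**3. Size under constant hazards.** Let h be the total hazard of a first event (progression or death), and f the share of first events that are deaths without documented progression.
- Median PFS with death counted: ln 2 / h.
- Median with deaths censored: ln 2 / [h(1−f)].
- Ratio: 1/(1−f).

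Both f and the true medians below are assumptions (months).

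| f | Factor | True 6 reads | True 8 reads | True 10 reads |
|---|---|---|---|---|
| 0 | 1.00 | 6.0 | 8.0 | 10.0 |
| 5% | 1.05 | 6.3 | 8.4 | 10.5 |
| 10% | 1.11 | 6.7 | 8.9 | 11.1 |
| 20% | 1.25 | 7.5 | 10.0 | 12.5 |
| 30% | 1.43 | 8.6 | 11.4 | 14.3 |

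**4. Small samples.** A Kaplan-Meier simulation used 4,000 trials per setting, an assumed true median of 8 months, uniform administrative censoring at 12 to 36 months, and assumed sizes of 12 and 18. Deaths without progression were either counted as events or censored at the date of death. The middle columns give the typical (median) estimate in months.

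| n | f | Death counted | Death censored | Trials where censoring gave the longer median |
|---|---|---|---|---|
| 12 | 5% | 7.1 | 7.7 | 27% |
| 12 | 10% | 7.1 | 8.2 | 45% |
| 12 | 20% | 7.1 | 9.6 | 74% |
| 12 | 30% | 7.1 | 11.2 | 88% |
| 18 | 5% | 7.4 | 8.0 | 38% |
| 18 | 10% | 7.4 | 8.5 | 61% |
| 18 | 20% | 7.4 | 9.8 | 86% |
| 18 | 30% | 7.4 | 11.5 | 96% |

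In no simulated trial was the deaths-censored median the shorter one.

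**5. Direction.** With censoring at the date of death, recoding a death as censored replaces a downward step by no step and leaves later risk sets unchanged. The curve can only stay level or rise. If last follow-up is instead dated to a visit before the death, the risk set shrinks slightly earlier, and a single small data set could dip below between that visit and the death. The upward direction therefore describes the quantity being estimated and is not a guarantee for every such sample.

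**The case against.** The strongest reply is that little depends on this. The trial is single-arm, and escalation rests on DLTs assessed at 90 days. The article sets no PFS hypothesis, threshold or go/no-go rule. Deaths are not lost either: all count in OS, and fatal IORT-related events are documented as serious adverse events. This stands, and it limits the severity.

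Second, f may be small. *Background* says that recurrence is local in virtually all cases, and after the early window tumour-related clinical decline is itself progression. Nothing in the document supports 20% or 30% in particular. This also stands: the upper rows of the tables show sensitivity and are not forecasts.

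Third, the article does not say how the last follow-up date is coded, and its OS sentence is equally silent on patients still alive. Censoring is the natural reading, but it is an inference. The cited RANO source is also not available here, so its treatment of death cannot be checked. The article's own lists do not mention death, and a reader should not need the source to know whether death is an event. Nor can the point be left to an unseen analysis plan, because the article prints an explicit definition.

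A reader might infer more than the text supports:
- That reported PFS will be too long. This requires at least one death without documented progression. Even at f = 5%, most simulated trials showed no change in the median.
- That early deaths rarely carry a progression date. The article gives no rates from which to judge this.
- That the result will be set against published PFS figures. No such comparison is planned in the article. It says only that the study should support later randomised trials.

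**Conclusion.** The definition is wrong as written: it describes time to progression and calls it PFS. Any resulting bias lengthens the estimate, and it vanishes if nobody dies without documented progression. Its size cannot be derived from the document. The range of 5% to 43% rests on the assumed f of 5% to 30% and on constant hazards. It measures the gap between the two endpoints and does not include any further distortion if patients close to death are also close to progression. This is a cheap correction to a secondary endpoint that leaves the MTD decision untouched. Treating it as a mandatory change would overstate it.

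**What to change.** Define PFS as the time from IORT to first RANO progression or death from any cause, whichever comes first, with patients alive and progression-free censored at their last adequate MRI assessment. If the present quantity is wanted, call it time to progression and report it under that name.

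The change is one sentence. Death dates are already needed for OS, and MRI precedes every quarterly follow-up visit, so no new data are required. The downside is that the reported PFS may be less favourable.

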### Early postoperative MRI

Early postoperative MRIs must be performed within a window of 24–48 h after surgery and must be analyzed in a standardized assessment. Before contrast application T1-hyperintense lesions must be used to evaluate residual blood/heme and T2-TSE, T2-FLAIR, and DWI to evaluate ischemia. After contrast application, T1-hyperintense masses or nodules (residual tumor tissue) have to be quantified and the following has to be documented:Complete resection: removal of at least 98% of the T1-enhancing lesions.Subtotal resection: removal of 88-98% of the T1-enhancing lesions.Partial resection: removal of less than 88% of the T1-enhancing lesions.

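### In the 12 weeks after EBRT, histology counts as progression only for new lesions, so tissue-proven regrowth of residual tumour is literally not a PFS event until later

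*Protocol article*

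**What the plan says.** The article's section on secondary end points sets a special rule for the 12 weeks after EBRT. The rule is closed and has two routes. The imaging route begins "In INTRAGO, only cases where new T1-enhancing lesions are detected", and such a lesion has to lie outside the 80% isodose. The other route relies on tissue: "new lesions that are histologically proven to be new manifestations of GBM are defined as true progression within a timeframe of 12 weeks after EBRT". Both routes need a new lesion.

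The reason given is that "irradiation transiently increases the permeability of the (peri)tumoral vasculature which in turn impairs the validity of MRI scans during this period". The wider criteria open only when the window ends: "After this period, progressive disease is defined if one of the following RANO criteria applies". They are new enhancement outside the field, growth of at least 25%, clinical deterioration due to tumour, and T2/FLAIR increase. The growth criterion compares scans "between the first post-radiotherapy scan, or a subsequent scan with smaller tumor size, and the scan at 12 weeks or later".

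Residual tumour is foreseen. Under Patient selection, "patients with tumors that are likely to be only partially removable are also eligible for the study", and the section on the early postoperative MRI has a category for it: "Partial resection: removal of less than 88% of the T1-enhancing lesions".

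**The concern.** In a patient with residual enhancing tumour, failure can take the form of growth of a lesion that is already there. If that lesion is re-operated inside the window and pathology shows mainly viable tumour, neither early route applies because the lesion is not new. The stated reason for caution is unreliable MRI. The rule already accepts tissue as the remedy for new lesions, but gives no reason for refusing it altogether for existing ones.

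The growth criterion adds a second effect. Debulking leaves a smaller lesion, and a later, smaller scan becomes the reference for the 25% rule. Re-operation, which is often itself a sign of failure, can then lengthen recorded PFS. At stake is the dating of some early PFS events, and so the PFS figures that later randomised trials may draw on.

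**Working it through.** The article states no figure for this point, so there is none to reproduce. The check reads the rule literally and then works out the dates.

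**Inputs from the article**
- EBRT starts within 4 weeks of IORT.
- 30 fractions are given, five per week. The last fraction falls 39 days after the first if treatment starts on a Monday and is not paused.
- The early window is 12 weeks (84 days) after EBRT.
- Post-EBRT visits with MRI are quarterly, taken here as weeks 13 and 26.
- Cohort safety is assessed at day 90 after IORT, and MRI is one of the bases for judging DLTs.

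**Literal scoring of an illustrative patient**
1. The residual lesion measures 20 × 20 mm on the postoperative MRI and 30 × 30 mm at week 8 after EBRT. Growth in the product is 900/400 − 1 = 125%.
2. The lesion is re-operated and is predominantly viable GBM.
3. The lesion is not new, so neither early route applies and there is no event.
4. The week-13 scan shows the smaller remnant and becomes the growth reference.
5. The first scheduled scan that can show 25% growth over that reference is at week 26.

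**Calendar for EBRT starting on day 28**
- EBRT ends: 28 + 39 = day 67.
- Week 8: 67 + 56 = day 123.
- Window closes: 67 + 84 = day 151.
- Quarterly scans: 67 + 91 = day 158 and 67 + 182 = day 249.
- Delay if only the growth rule scores: 249 − 123 = 126 days.
- Delay if clinical deterioration or T2/FLAIR increase scores as the window closes: 151 − 123 = 28 days.

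**Delay by week t of re-operation** (12 − t, 13 − t and 26 − t weeks; this does not depend on the EBRT start date)

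| t | scored at window close | scored at week-13 scan | scored at week-26 scan |
|---|---|---|---|
| 4 | 8 weeks (1.8 months) | 9 weeks (2.1) | 22 weeks (5.1) |
| 8 | 4 weeks (0.9) | 5 weeks (1.1) | 18 weeks (4.1) |
| 10 | 2 weeks (0.5) | 3 weeks (0.7) | 16 weeks (3.7) |

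**Effect on median PFS, under assumptions only.** Assume exponential PFS with a median of 7 months. Assume that 10%, 25% or 50% of progressions between days 67 and 151 are re-operated residual growth. None of these values is in the article. Average rise in the sample median (20,000 simulated trials):

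| Patients | Re-dated to window close or first quarterly scan | Re-dated to day 249 or 91 days after the event, whichever is later |
|---|---|---|
| 9 | about 1 to 6 days | about 6, 14 and 25 days |
| 18 | about 1 to 5 days | about 7, 16 and 28 days |

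**The case against.** The strongest objection is that histology shows tumour is present, not that it has grown. A partially resected patient had viable GBM in that lesion from the start, so finding it again is expected even when the enlargement is treatment effect. The growth itself still rests on MRI in the period the article calls unreliable. This stands in part. Viable cells in a known remnant are weaker evidence than in a new lesion, so a reader should not infer that the rule scores identical evidence differently by extent of resection. It does not justify ignoring documented growth when pathology shows mainly viable tumour rather than treatment effect.

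A reader might also infer that such events are always months late, or cannot be recovered. The article does not support that: clinical deterioration and T2/FLAIR increase can score once the window closes, and the minimum delay at week 8 is about 4 weeks.

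The week-8 scan in the example is unscheduled, which is fair. But with EBRT starting between days 14 and 28 and no pause, day 90 falls (90 − 53)/7 = 5.3 to (90 − 67)/7 = 3.3 weeks after EBRT, so the safety assessment lies inside the window. The article also lists surgical debulking among the options for suspected necrosis with mass effect or symptoms, so tissue may be obtained then.

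Finally, the phrase about new manifestations might be meant to include regrowth. The clause still begins with new lesions. If regrowth was intended, the same sentence needs editing.

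**Conclusion.** The point holds as a gap in the definition of a secondary endpoint. Taken literally, tissue-proven regrowth of residual tumour in the 12 weeks after EBRT is not progression, and no other section of the article restores it. The event is late by at least 12 − t weeks. The 126 days is a worst case for the week-8 example: it needs the growth rule alone to score, with the first quarterly scan as the reset reference. Earlier re-operation gives longer delays.

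The subgroup is narrow: residual enhancing tumour, growth within the window, re-operation, and predominantly viable tumour in the specimen. The article does not give its size, so the simulated shifts show possible scale only and do not establish that reported PFS is materially overstated. The MTD, the DLT rules and OS are unaffected. This is a minor point, worth correcting because the correction is cheap.

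**What to change.** 1. Extend the histology limb to read, in substance: *or a new or existing enhancing lesion with documented growth whose histology shows predominantly viable GBM rather than treatment effect*. Name the reference scan and the growth threshold.
2. Date the event at the scan that led to the operation.
3. State that a scan after re-operation for such a lesion does not reset the reference for the 25% rule.
4. Keep unproven in-field enhancement growth excluded during the window, as now.
5. Report PFS under the plan's current wording as a sensitivity analysis, because the evidence from a known remnant is weaker.

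The cost is a short edit to the PFS definition and one extra analysis. It uses the mandatory postoperative MRI, and scans and pathology from operations done anyway. Reported PFS may be slightly shorter, and an occasional treatment-related enlargement with surviving tumour could be counted as progression.
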